4.5 END OF STUDY DEFINITION

Patients will complete the study when they are discharged from the acute care facility in which they received the COVID-19 convalescent plasma or 30 days after most recent convalescent plasma transfusion whichever comes first.

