**Statistical Analysis Plan (version 2.0)**

**Data set description:** As of **5/28/2020**, there are 17,155 transfusions. We estimate approximately 15,000 of these will have data through Day 7 by the end of next week. Outcome data through Day 30 will be available on a much smaller set of patients, and given the interval censoring between Day 7 and Day 30 with the current data structure, analyses for this analysis report will focus on all-cause mortality through Day 7.

**Primary Hypothesis:** Antibody concentration level in transfused plasma will establish a dose-response relationship with overall survival in patients with COVID-19 treated with convalescent plasma.

**Secondary Hypothesis:** The effect of antibody concentration level will serve as an effect modifier in the presence of baseline measures of disease severity and pre-disposing risk factors.

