## Statistical Hypotheses

**Primary Hypothesis:** 7-Day and 30-Day mortality will be affected by plasma transfusion dynamics after adjustment for pre-disposing risk factors. Transfusion dynamics are defined in the context of timeliness of transfusion relative to date of diagnosis, the volume of plasma initially given (i.e., on the first transfusion day), and the quantity of neutralizing antibodies on the first day of transfusion.

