## Primary Analysis Plan

### Preparation of the survival endpoint: The timing of death is recorded only with the precision of a calendar day, so adjustments are needed to develop the survival estimates. For deaths that occur on the same day of transfusion, a death indicator representing 0.5 days will be administratively assigned. Otherwise, the number of days between the date of the first transfusion and death will be calculated for each participant. For patients transfused without a death record recorded as an SAE, or more precisely, on the death case report form, they are assumed to be alive. Within the context of the report and programming, this is denoted as the "immortal" survival assumption. To minimize extrapolation of the survival curves beyond a reasonable time that this assumption could be upheld, survival estimates are limited to 30 days; however, the report does introduce stopping the survival curves early, for example, at Day 7 for 7-Day mortality estimates.

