Crude mortality and 95% (score) confidence intervals (CI) are calculated for the overall cohort and additionally, by some of the key variables of interest. Given the study is non-randomized and multiple sources of confounding are potential present in the data, adjusted estimates are also provided in the report. The approach for adjusted estimate is as follows:

- A baseline Cox regression model is fit to the data. Without loss of generality, assume there is one variable of direct interest (e.g., volume of plasma transfusion) and a set of covariates that are desired to be controlled for in the estimate.
- Using the 'conditional' method for estimating adjusted survival curves (https://cran.r-project.org/web/packages/survival/vignettes/adjcurve.pdf), an adjusted estimate of the mortality is obtained. This process allows for estimation of an expected survival at a particular point in time (e.g., at 30 days).
- To estimate the confidence interval for the adjusted survival curve, the bootstrap is used. For each of the replicates performed, the original data object is used to determine the reference distribution for standardized mortality estimates.
- The approach was extended to provide an estimate of the relative risk over one or more variables of interest. A posterior distribution of potential relative risks was constructed by a cartesian merge of the posterior adjusted survival estimates for each group. The 2.5th and 97.5th percentiles of this distribution were used as the bootstrap confidence interval for the relative risk. No p-values are provided for this method. In events where statistical inference is desired, the hazard ratio and associated significance test should be utilized.

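### SAP v5.0 counts every transfused patient without a death form as alive to Day 30 and states no minimum follow-up, so immature or unreported follow-up is recorded as survival

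*Supplement*

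**What the plan says.** The primary hypothesis of SAP v5.0 (Statistical Hypotheses) is that "7-Day and 30-Day mortality will be affected by plasma transfusion dynamics after adjustment for pre-disposing risk factors". Under Preparation of the survival endpoint, a transfused patient with no death recorded "on the death case report form, they are assumed to be alive", which the SAP itself names the 'immortal' assumption. The only limit placed on it is that "survival estimates are limited to 30 days", with curves stopped at Day 7 for the 7-day estimate.

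The same endpoint feeds everything downstream. "Crude mortality and 95% (score) confidence intervals (CI) are calculated for the overall cohort" and by key variables, and the Cox models, adjusted curves and bootstrap relative risks use it too. SAP v5.0 states no data cut-off, minimum time since transfusion, reporting lag, censoring at last contact, completeness report or sensitivity analysis for this rule.

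Protocol v10.0, Section 4.5, ends a patient's participation at discharge from the treating facility "or 30 days after most recent convalescent plasma transfusion whichever comes first".

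**The concern.** The rule turns unknown status into observed survival for two kinds of patient: those transfused too recently to have reached the horizon, and those whose death was never entered. The Day-30 cap prevents extrapolation beyond Day 30, but a patient transfused three days before data lock is still carried alive to Day 30. Apart from a death recorded in error, the rule can only lower mortality. The score intervals then treat such patients as known survivors.

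At stake are the absolute mortality figures, crude and standardised, and possibly the three comparisons in the primary hypothesis. Volume is the clearest route to a comparative bias. Protocol Section 10.5 shows that one to two units were allowed from 15 April 2020 and multiple doses from 15 May 2020, so volume may be tied to calendar time and hence to length of follow-up.

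**Working it through.** The plan gives no mortality, event count or completeness figure for this analysis, so there is nothing to reproduce. Only step 1 uses document figures alone; the rest are illustrations under the assumptions named.

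**1. Evidence on completeness.** SAP v2.0 (Data set description, 28 May 2020) counted 17,155 transfusions and expected about 15,000 to have Day-7 data by the end of the following week: (17,155 − 15,000)/17,155 = 2,155/17,155 = 12.6% without. For Day 30 it says only "Outcome data through Day 30 will be available on a much smaller set of patients".

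**2. If deaths went missing at that same rate (assumption).** Apparent mortality = true mortality × share of deaths captured. At 0.874, 10% becomes 8.7% and 20% becomes 17.5%. With 20% mortality among patients of known status, the possible range runs from 0.20 × 0.874 = 17.5% (all unknowns alive) to 0.1749 + 0.1256 = 30.0% (all dead). Treating the 17,155 as patients, a 95% interval at 17.5% is about ±1.96 × √(0.175 × 0.825/17,155) = ±0.6 points, which reflects none of that range.

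**3. Immaturity.** Let f be the share with follow-up uniform on 0–30 days. Observed mortality = (1 − f) × p30 + f × mean F(u). With p30 = 25% and Weibull deaths of shape 0.8, mean F = 14.5%.
- f = 0.2: 0.8 × 25 + 0.2 × 14.5 = 22.9%
- f = 0.5: 0.5 × 25 + 0.5 × 14.5 = 19.8%

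A simulation assumed uniform entry from 4 April (IRB approval) to 27 July 2020 (date of SAP v5.0), 114 days, with constant hazard, true 30-day mortality 20% and 40,000 patients. About 30/114 = 26% had under 30 days. The rule gave 17.8%; the product-limit estimate, censoring at end of follow-up, gave 20.4%. Restricting entry to at least 30 days before the cut gave 19.7% by either method. Simulation error is about 0.2 points.

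**4. Comparisons.** Apparent RR = true RR × (capture in B / capture in A). All cases below have true RR 1.
- Step 3 model, 30% versus 10% recent: (0.7 × 25 + 0.3 × 14.5)/(0.9 × 25 + 0.1 × 14.5) = 21.85/23.95 = 0.91.
- Simulated late-half versus early-half entrants, an extreme contrast: 14.7%/19.8% = 0.74.
- Mortality 20%, 7,500 per group, capture 95% versus 90%: RR 0.947, and a two-sided 5% test rejects 35% of the time. Capture 95% versus 85%: RR 0.895, rejects 89%.
- Equal capture: RR stays at 1.

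**5. Would censoring at last contact be unbiased?** Assume every death is captured, with 10% dead by Day 7 and 25% by Day 30. Of 100 patients, 90 are alive at Day 7, 15 die later and 75 survive. If a share c of survivors has only a Day-7 form and is censored there, mortality = 1 − 0.90 × [1 − 15/(90 − 75c)].
- c = 0.2: 28.0%
- c = 0.3: 30.0%
- c = 0.5: 35.7%

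So this method can overstate mortality when survivors' forms lag behind death reports. It recovered the truth in step 3 because censoring there came only from staggered entry.

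**The case against.** Deaths come through a separate death form tied to SAE reporting, which Protocol Sections 8.2 and 8.3 make mandatory whatever the judged relation to plasma. Section 7.3 anticipates no loss to follow-up. The assumption is openly named and capped, and Section 9.1 calls all analyses exploratory. SAP v5.0 is silent on the data lock rather than ruling out a mature cohort; if the analysed cohort was mature, the recency part vanishes, and for 7-day mortality that takes only seven days plus any reporting lag.

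Much of this stands, and it rules out three stronger readings.
- A reader might infer that 12.6% of deaths were missed. The figure is a forecast of routine Day-7 data at an earlier cut. It may reflect a temporary lag, and a missing Day-7 form is not a missing death form.
- A reader might infer that the groups are in fact affected unequally. No section gives completeness or recency by timing, volume or titre. Equal under-capture leaves relative risks about unchanged. Calendar month, listed under Risk Modifiers, could remove part of any difference if it enters the primary model, which the SAP does not say.
- A reader might infer that censoring at last contact should simply replace the rule. Step 5 shows that it can err in the other direction.

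What does not stand is the view that mandatory reporting settles the matter. A duty to report does not establish completeness, and it cannot capture a death that has not yet occurred at data lock. Adjustment for calendar month does not restore the absolute level. Exploratory or not, the SAP names a primary hypothesis and directs inference to the hazard ratio.

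**Conclusion.** The concern holds for absolute mortality. Followed as written, the rule understates 7-day and 30-day mortality to the extent that immature or unreported patients are included, and the intervals omit that uncertainty. For the hazard ratios and relative risks the concern is conditional on group differences that the documents neither show nor exclude.

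The actual size cannot be derived from the documents. Under the assumptions in the working, 30-day mortality falls by roughly 2 to 5 points (25% to 22.9% or 19.8%; 20% to 17.8%), and modest differences in capture are enough to create a false difference at large sample sizes.

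A separate limit remains even with a mature cohort. Because participation can end at discharge, a live discharge does not establish survival to Day 30. For discharged patients the estimate is in effect in-hospital mortality to Day 30.

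**What to change.** Amend Preparation of the survival endpoint in the SAP:

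1. State the data lock. Restrict the 30-day (7-day) analysis to patients first transfused at least 30 (7) days plus a fixed reporting lag before it.
2. Report, by timing, volume and titre group, the share without documented vital status at Day 7 and Day 30.
3. Within the mature cohort, label the 'immortal' result as the lower bound on mortality. Beside it, give a sensitivity analysis that censors patients without a death form at the last date documented alive, noting that this may overstate mortality if deaths are reported more completely than survivors' forms.
4. State that deaths after discharge need not be captured under Protocol Section 4.5, and describe the estimate accordingly.

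The cost is SAP wording and a rerun. SAP v2.0 already planned to use the daily summary and Day-7 assessment for known vital status, so the dates should be available. The most recent patients leave the 30-day set, and reported mortality may be less favourable.

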### Primary Data Analysis: The primary analysis will be conducted through a series of unadjusted and adjusted survival models. This is required given the study is non-randomized and factors that may affect overall survival may serve as a confounding variable in the analysis. The primary hypothesis presents three variables that are hypothesized to have an impact on mortality.

First, the time to transfusion is considered. Based on early reports with convalescent plasma, a target window of 0 days, 1-3 days was considered optimal. Therefore, patients are divided into a group representing "timely" delivery of convalescent plasma. The remaining subjects are split into two groups, Days 4-10 (i.e., a week following a timely period) and Days 11+. In some analyses to aide in the graphical presentation of the data, the timeliness data is dichotomized into <=3 days vs. 4+ days.

Second, the transfusion volume on the first day of transfusion (if more than 1 transfusion was given). For this analysis, various categorizations of the volumes were considered, however, for the primary analysis, a spilt at 225 ml was implemented. This effectively separates people that received 1 unit (~ 200ml) from those that deliberately received more than 1 unit of plasma. 225 ml was selected to all for some variance in the volume in the first unit of plasma.

For the final component of the analysis, the neutralizing antibodies are both semi-quantitative and categorical in interpretation. There are lab established thresholds for negative (<1:80) and serial dilution allows for estimates ranging from 1:80 to >=1:2560. The analysis will consider the levels of the titers as nominal values as well as introducing some thresholds to classify the titers into a "low" vs. "high" classification. The original statistical analysis plan consisted of a planned analysis of the titer data using a splined fit on the observed antibody concentration. The spline was to avoid a strong linear assumption on the relationship of the titer and survival. The decision to use that approach was changed post hoc to the dichotomized approaches to account for the lack of dose-response relationship observed with the data. This decision allowed for simplification of the data presentation.

Crude mortality and 95% (score) confidence intervals (CI) are calculated for the overall cohort and additionally, by some of the key variables of interest. Given the study is non-randomized and multiple sources of confounding are potential present in the data, adjusted estimates are also provided in the report. The approach for adjusted estimate is as follows:

- A baseline Cox regression model is fit to the data. Without loss of generality, assume there is one variable of direct interest (e.g., volume of plasma transfusion) and a set of covariates that are desired to be controlled for in the estimate.
- Using the 'conditional' method for estimating adjusted survival curves (https://cran.r-project.org/web/packages/survival/vignettes/adjcurve.pdf), an adjusted estimate of the mortality is obtained. This process allows for estimation of an expected survival at a particular point in time (e.g., at 30 days).
- To estimate the confidence interval for the adjusted survival curve, the bootstrap is used. For each of the replicates performed, the original data object is used to determine the reference distribution for standardized mortality estimates.
- The approach was extended to provide an estimate of the relative risk over one or more variables of interest. A posterior distribution of potential relative risks was constructed by a cartesian merge of the posterior adjusted survival estimates for each group. The 2.5th and 97.5th percentiles of this distribution were used as the bootstrap confidence interval for the relative risk. No p-values are provided for this method. In events where statistical inference is desired, the hazard ratio and associated significance test should be utilized.

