1.2 SCHEMA

**Study Schema**

Eligibility Criteria Met

Inclusion Criteria

1. At least 18 years of age (if less than 18 years contact FDA for emergency IND authorization)
2. Laboratory confirmed or clinically suspected diagnosis of infection with SARS-CoV-2*
3. Admitted to an acute care facility for the treatment of COVID-19 complications
4. Severe or life threatening COVID-19, or judged by the treating provider to be at high risk of progression to severe or life-threatening disease
5. Informed consent provided by the patient or healthcare proxy

*Patients enrolled based on clinically suspected infection with SARS-CoV-2 should have pending laboratory

confirmation.

| **Severe disease defined as any of the following:** | **Life-threatening disease defined as any of the following:** |
| --- | --- |
| - dyspnea - respiratory frequency> 30/min - blood oxygen saturation ≤ 93% - partial pressure of arterial oxygen to fraction of inspired oxygen ratio < 300 - lung infiltrates > 50% within 24 to 48 hours | - respiratory failure - septic shock - multiple organ dysfunction or failure |

Informed consent obtained from patient or healthcare proxy

Blood type obtained at local laboratory per local institutional procedures and policies Patient Registered with American Red Cross or other blood source by uscovidplasma.org.

Transfusion with appropriate COVID-19 convalescent plasma per institutional transfusion protocol

Patients may be premedicated with acetaminophen and diphenhydramine, per local practice

Recommended administration rate for plasma administration should follow best clinical practice procedures for the patient’s unique condition and your facility guidelines. r

Serious adverse events observed by the treating physician or reported by patient to provider Reporting of patient demographics and acute care resource utilization

Information entered on COVID-19 Plasma Expanded Access Program secure website (Information on plasma unit administered will be obtained directly from blood collector)

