6.1.2 DOSING AND ADMINISTRATION

For practical purposes in the current outbreak, one – two units of COVID-19 convalescent plasma will be

administered. This will be provided by a registered or licensed blood collector and will be collected preferably by apheresis (total volume of plasma to be administered will be approximately 200 mL or more), or if necessary, by conventional methods (volume of plasma to administer approximately 200- 250 mL per unit). Individual institutional guidelines for the administration of plasma should be followed, including the use of any premedications, such as acetaminophen and diphenhydramine.

**If a subsequent unit of convalescent plasma is transfused**, the treating physician will begin the transfusion at a time that is clinically compatible with the patient’s underlying condition.

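### The 225 mL first-day split is a volume contrast; the protocol's unit volumes do not support reading it as one unit versus more than one

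*Supplement*

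**What the plan says.** SAP v5.0, Statistical Hypotheses, names three transfusion variables that may affect 7-day and 30-day mortality. One is "the volume of plasma initially given (i.e., on the first transfusion day"). The Primary Data Analysis section reports that "various categorizations of the volumes were considered" and that "for the primary analysis, a spilt at 225 ml was implemented". It gives the reason, "225 ml was selected to all for some variance in the volume in the first unit of plasma", and states what the split achieves: "This effectively separates people that received 1 unit (~ 200ml) from those that deliberately received more than 1 unit of plasma". The Secondary Data Analysis section keeps the unit reading. Its strata are formed from infusion volume, yet its example stratum is described as patients given two units.

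Protocol v10.0, section 4.3, puts one unit at approximately 200 mL. Section 6.1.2 gives a range for the fallback collection route: "or if necessary, by conventional methods (volume of plasma to administer approximately 200- 250 mL per unit"). For apheresis, the preferred route, it gives only a total of about 200 mL or more, with no upper limit per unit. The schema in section 1.2 adds: "Information on plasma unit administered will be obtained directly from blood collector".

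**The concern.** The separation claim needs nearly all single units to be at or below 225 mL. The protocol's range for a conventional unit runs 25 mL past that point, and for apheresis there is no stated ceiling to compare with. Some patients given one conforming unit would then be counted among those said to have deliberately received more.

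First-day volume is one of the three exposures in the primary hypothesis, and the SAP uses plasma volume as its example variable when it describes the adjusted mortality estimates. If the result is reported as one unit against two or more, part of the upper group does not fit the label, and the contrast between unit groups is diluted by an amount that nobody has measured.

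**Working it through.** The plan gives no figure to reproduce here. It states no distribution of unit volumes, no split by collection route and no count of patients by number of units. The check compares the cut with the stated volumes, then sizes the error under stated assumptions.

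**1. Where the cut falls.** Conventional unit: 200 to 250 mL (protocol 6.1.2). Midpoint: (200 + 250)/2 = 225 mL, which is the cut. The SAP's allowance above a 200 mL unit is 225 − 200 = 25 mL, half of the 50 mL range. Two conventional units total 2 × 200 = 400 mL to 2 × 250 = 500 mL. For conventional units, then, nothing falls between 250 and 400 mL, and the cut sits inside the one-unit range rather than in that gap.

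**2. Share *f* of single units above 225 mL (assumed distributions).**
- Uniform on 200 to 250: (250 − 225)/50 = 50%.
- Normal, mean 200: 1 − Φ((225 − 200)/SD), which gives 0.6%, 4.8%, 10.6% and 15.9% for SD 10, 15, 20 and 25.
- Normal, mean 210, SD 15: 1 − Φ(15/15) = 15.9%.

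**3. Effect on a contrast read as units.** Assume 60% of patients truly received one unit on the first day, all patients with more exceed 225 mL, mortality is 25% with one unit and 20% with more (true RR 0.80), and crossing the cut is unrelated to prognosis. The group at or below 225 mL is then all one-unit patients, at 25%. One-unit share of the upper group: c = 0.6*f*/(0.4 + 0.6*f*). Apparent RR = 0.80 + 0.20*c*.

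| *f* | *c* | Apparent RR |
|---|---|---|
| 0.6% | 0.0036/0.4036 = 0.9% | 0.80 |
| 4.8% | 0.0288/0.4288 = 6.7% | 0.81 |
| 15.9% | 0.0954/0.4954 = 19.3% | 0.84 |
| 25% | 0.15/0.55 = 27.3% | 0.85 |
| 50% | 0.30/0.70 = 42.9% | 0.89 |

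The 25% row is an intermediate value and comes from none of the distributions above. At *f* = 50%, mortality in the upper group is 0.429 × 25% + 0.571 × 20% = 22.1%. The absolute difference is 2.9 points instead of 5, or 57% of it.

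**4. Another unit mix.** With 65% on one unit, c = 0.65*f*/(0.35 + 0.65*f*), and the apparent RR is 0.82 at *f* = 5%, 0.83 at 10% and 0.90 at 50%. The pattern is the same.

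**The case against.** The strongest reply is that the exposure in the hypothesis is volume, not number of bags. A patient given 240 mL belongs in the group above 225 mL, and dilution arises only if the result is read as units. That stands: the volume comparison is sound as such, and the fault lies in the interpretation the SAP attaches to it.

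Second, the 200 to 250 mL range covers only the collection route used if necessary, while both documents place a typical unit near 200 mL and the SAP did allow for variation. This also stands, and it limits what can be said about size. With volumes centred on 200 mL and an SD of 10 to 25 mL, the share is 0.6% to 15.9%. It does not rescue the separation claim, because the preferred route has no stated per-unit maximum at all.

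Third, the protocol (sections 9.1 and 9.4) calls the analyses exploratory. That lowers the stakes but does not make the description of the exposure accurate.

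A reader might also infer that the cut was chosen by looking at mortality. The documents do not support this. The SAP says that other categorizations were considered, gives a reason for 225 mL that does not involve outcome, and uses the term post hoc for the titer change only. Whether the choice was made without sight of outcome is simply not stated.

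**Conclusion.** The SAP's statement that 225 mL effectively separates one unit from more than one is not supported by the protocol's own unit volumes. An unquantified share of one-unit patients falls in the upper group: under 1% to 50% on the distributions assumed here. The 50% is the top of the range examined rather than a proven ceiling, since apheresis units have no stated limit. Read as units, a true RR of 0.80 would appear as about 0.80 to 0.89 with 60% on one unit. Attenuation is assured only if misclassification is unrelated to prognosis. If unit size varies with supplier or site, and these vary with patient risk, the direction is uncertain.

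A reader might go further and conclude that many one-unit patients are misclassified, or that the primary volume contrast is invalid. Neither follows. The documents give no volume distribution from which to show many, and the contrast holds as a comparison of volumes.

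**What to change.** Before looking at outcome, cross-tabulate first-day volume against number of units, by collection route if known, using the blood-collector information where available. Then choose one of two definitions and state it:

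- **Units:** classify by recorded count on the first day, 1 versus 2 or more. If apheresis units vary widely in size, this answers a different question from the volume hypothesis, and the SAP should say so.
- **Volume:** keep 225 mL, describe it as volume only, delete the separation sentence, and reword the two-unit example in the Secondary Data Analysis section.

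In either case add first-day volume as a continuous exposure with a spline, and a sensitivity analysis with a cut above 250 mL. That cut should not be the main repair, because no single-unit maximum is stated for apheresis.

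The cost is SAP wording, one recoded variable and a little extra analysis, and some patients will change group. The schema says that unit information comes from the collector but does not confirm that first-day unit counts are in the analysis data. If they are not, the volume wording plus the two added analyses is the minimum.
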